## Abstract

**Background:**

Only a minority of all alcohol- and drug abusers is receiving professional care. In an attempt to narrow this treatment gap, treatment facilities experiment with online healthcare. Therefore, it is important to test the (cost-)effectiveness of online health interventions in a randomized clinical trial.

**Methods:**

This paper presents the protocol of a three-arm randomized clinical trial to test the (cost-) effectiveness of online treatment for problem drinkers. Self-help online, therapy online and a waiting list are tested against each other. Primary outcome is change in alcohol consumption. Secondary outcome measures include quality of life and working ability. Incremental cost-effectiveness ratios for self-help online alcohol and therapy online alcohol will be calculated. The predictive validity of participant characteristics on treatment adherence and outcome will be explored.

**Discussion:**

To our best knowledge, this randomized clinical trial will be the first to test the effectiveness of therapy online against both self-help online and a waiting-list. It will provide evidence on (cost-) effectiveness of online treatment for problem drinkers and investigate outcome predictors.

**Trial registration:**

This trial is registered in the Dutch Trialregister (Cochrane Collaboration) and traceable as NTR-TC1155.

## Background

The Netherlands have, compared to most other countries, a fairly accessible network of substance abuse treatment centres (SATCs). However, the target population of these SATCs is not sufficiently addressed: Only a minority of all current alcohol- and drug abusers is receiving professional care [1]. This so-called treatment gap is mainly due to two reasons. As substance dependence is strongly stigmatized, the threshold to visit a treatment centre is high [2]. And as most SATCs offer outpatient facilities during working hours only, many people with jobs cannot find to attend SATCs face-to-face therapy.

Another challenge to healthcare in general and addiction treatment in particular is optimising cost-effectiveness. As the future health spending is expected to increase at a much higher rate than in the past [3,4], cost-effectiveness is an important parameter in the development of new treatment programs. In general, early interventions, preventive care, and disease self-management, together with the correct implementation of health information technology and internet applications, is believed to have the potential to enhance health status while improving efficiency and reducing healthcare costs [3].

Substance abuse treatment over the internet has the potential to address these issues: The influence of both stigmatization and restricted opening times of healthcare institutions is reduced when clients do not have to visit a SATC during working hours, but can visit their web-based treatment environment from any place and at any time. Earlier evaluations have shown that a majority of online substance abuse treatment participants manage to hold their jobs [5,6]. Therefore, improvement in job performance may be expected as a result of successful participation, as problematic drinking habits tend to interfere with working ability in general.

The increasing number of online treatment options worldwide shows that treatment facilities are willing to experiment with online healthcare. A review of the current state of the art in substance abuse treatment over the internet is promising [7]. Some authors report online substance abuse treatment to be successful in addressing an underserved population [5,6]. Results of the first randomized clinical trials support the use of the internet to extend the treatment options for substance abusers [8-10]. There is preliminary evidence on the cost-effectiveness of early interventions and computer-aided therapy for alcohol related problems [11,12]. However, as the number of randomized clinical trials for online substance abuse treatment is still sparse, its (cost-)effectiveness is yet to be supported more firmly. This article presents a randomized clinical trial that will extend the knowledge on effectiveness and cost-effectiveness of online treatment for problem drinkers.

The SATC whose interventions are subjected to this trial has pioneered in the development of internet applications for problematic alcohol and substance users. Since 2003, its online treatment programs have been based on two evidence-based techniques: cognitive-behavioural therapy (CBT) and motivational enhancement training. These early experiences have led to the development of online interventions for alcohol-, cannabis-, cocaine- and tobacco-users, and for pathological gamblers. Two online treatment programs for problem drinkers will be compared in this trial. One is an anonymous, online, non-counsellor involved, fully automated self-guided treatment program, referred to as Self-help Online Alcohol (SOA). The other is a real time, online, non anonymous, counsellor-guided therapy program for problem drinkers referred to as Therapy Online Alcohol (TOA).

SOA introduces participants to various CBT elements as a means to monitor and help them change their alcohol consumption. Registration of alcohol consumption, online diary, goal setting, and relapse prevention are among them. A recent study has shown that SOA is highly attractive and promising in its effects [6]. However, participants of SOA did report they missed the opportunity to interact with a counsellor on a regular basis. In response to the participants' suggestions, the online therapy program (TOA) has been developed. Like SOA, TOA is based on CBT and motivational enhancement training, but has a more intensive and stricter structured treatment course and regular counsellor interaction. Contact between client and counsellor takes place online in a one-on-one, private chat-room. TOA resembles to a great extent the conventional face-to-face manual based CBT training program [13], used in many SATCs in the Netherlands. Treatment elements of TOA include consumption registration, online diary, tailored feedback of recent alcohol consumption, contemplating advantages and disadvantages of drinking, goal setting, self-control methods, investigating risk-situations, coping with craving, emotions and social pressure, and the formulation of emergency plans in case of relapse. These elements are introduced by the counsellor. Working with the treatment elements is part of clients' weekly homework assignments.

The most important difference between SOA and TOA are seven real-time, one-on-one chat sessions with an experienced counsellor trained in TOA. Each chat session lasts for approximately 40 minutes. During these sessions, feedback on homework assignments is provided and the client is motivated to enhance his or her attempt to stop or reduce drinking. Because of it's interactive nature, chat-sessions resemble to a big extent the conversational dynamics of regular, face-to-face therapy contacts. This new element meets the expressed needs of participants of SOA and makes the intervention more similar to the successful face-to-face CBT treatment.

## Methods

### Aims of the trial

This study aims to test the effectiveness and cost-effectiveness of SOA and TOA against a waiting list control group, in a three-arm randomized clinical trial. Primary outcome measure is the change in alcohol consumption from baseline (t0) to the three month follow-up (t1) and to the six month follow-up (t2). Secondary outcome measures are changes in AUDIT scores, quality of life and quality of functioning at work. Incremental cost-effectiveness ratios for SOA and TOA will be calculated. The predictive validity of participant characteristics on treatment adherence and outcome will be explored.

### Study population

Our study population will be recruited through the SATCs website, that was viewed by 650.000 unique visitors in 2007 [14]. If necessary, additional attention for this study will be attracted through advertisements at family doctors' offices, internet-forums, and news-paper adds. Applicants meeting inclusion criteria defined in Table 1 are invited to participate.

**Table 1 T1:** Selection criteria for inclusion

**Inclusion criteria**	**Exclusion criteria**
age 18 – 64	prior therapy in addiction treatment centre
internet at home	history of alcohol delirium
AUDIT score > 8	history of drug overdose
alcohol consumption > 14 standard units per week	severe coronary problems
informed consent received	severe intestine diseases
	diagnosed schizophrenic
	history of stroke
	epilepsy in last year
	contemplated or attempted suicide in last year
	cocaine and or amphetamine use > 4 days last month
	cannabis use > 9 days last month
	holiday/travelling intention > 2 weeks during trial

### Research questions

Q1a. Do TOA participants reduce their alcohol consumption from t0 to t1 and t2 to a larger extent than SOA and waiting list control participants?

Q1b. Do TOA participants improve to a larger extent on secondary outcome measurement scores from t0 to t1 and t2 than SOA and waiting list control participants?

Q1c. Are TOA participants more often treatment-responders than SOA and waiting list control participants at t1 and t2?

Q1d. Do SOA participants reduce their alcohol consumption to a larger extent from t0 to t1 and t2 than waiting list control participants?

Q1e. Do SOA participants improve on secondary outcome measurement scores from t0 to t1 and t2 to a larger extent than waiting list control participants?

Q1f. Are SOA participants more often treatment-responders than waiting list control participants at t1 and t2?

Q2. What are the comparative costs per quality adjusted life year (QALY) for SOA and TOA?

Q3a. How do participants' demographic characteristics relate to demographics of participants in conventional face-to-face CBT programs?

Q3b. Do scores of working alliance between TOA participants and counsellor predict treatment-response at t1 and t2?

### Hypotheses

We hypothesize TOA participants will have reduced their alcohol consumption significantly more at the three month follow-up (t1) compared to SOA and waiting list control participants (Q1a). Between t0 and t1, we also expect TOA participants to improve on secondary outcome measurements (quality of life and working abilities) significantly more than SOA and waiting list control participants (Q1b). We hypothesize that a larger percentage of TOA participants will meet the criteria for treatment-responders compared to SOA and waiting list control participants (Q1c). We hypothesize that SOA participants will have reduced their t0 alcohol consumption significantly more at t1 than waiting list control participants (Q1d). Between t0 and t1, we also expect SOA participants to improve on secondary outcome measurements significantly more than waiting list control participants (Q1e). Finally, we hypothesize that a larger percentage of SOA participants will meet the criteria for treatment-responders compared to waiting list control participants (Q1f).

Between t1 and t2, we expect TOA participants to be better able than SOA participants to maintain their achieved changes in alcohol consumption, resulting in a significant time (t1–t2) by group (SOA-TOA) interaction. Alcohol consumption in SOA will be significantly higher at t2 compared to t1, whereas alcohol consumption in TOA will not change significantly during this period.

For question 2, we hypothesize that from t0 to t1 both the costs and the gains in QALY for SOA to be lower than the costs and the gains in QALY for TOA. As this means that both the numerator and the denominator of the cost-effectiveness equation is larger for TOA compared to SOA, we have no preconceptions of whether the incremental cost-effectiveness calculation will favour either SOA or TOA (Q2).

For question 3, we hypothesize our participants to be higher educated, a larger percentage to be working and female, compared to conventional outpatient SATC clients (Q3a). We also hypothesize that higher scores on working alliance will predict a larger proportion of treatment-response at t1 for TOA participants (Q3b).

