### Power calculation

Appropriate sample size is estimated using Gpower v.3.0.5 software [34]. This calculation is based on the primary outcome measure (alcohol consumption), in a one-way ANOVA test design. Based on [10] we expect an effect-size of *d *= 0.40 when comparing waiting list control and treatment groups. To be able to detect even smaller differential effects (*d *= 0.25) between SOA en TOA with *α *= .05 and *β *= .20, we aim to include 150 participants. The power calculation is summarized in Table 3.

**Table 3 T3:** Power analysis

F tests – ANOVA: Fixed effects, omnibus, one-way		
Analysis:	A priori: Compute required sample size	
Input:	Effect size f	0.25
	α error probability	0.05
	Power (1-β error probability)	0.80
	Number of groups	3
Output:	Non-centrality parameter λ	9.938
	Critical F	3.054
	Numerator df	2
	Denominator df	156
	Total sample size	159
	Actual power	0.805

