### Randomization

After the t0 measurement is completed, participants are allocated to one of the three trial arms. Because this randomized clinical trial is internet-based, we will organize the allocation procedures online as well. As the number of participants we aim to include in each trial arm (*n *= 50) is not very large, random variation in baseline characteristics could reduce group equivalence. Online, server-based performance of randomization procedures comes with the advantage of being able to implement stratified allocation or allocation through adaptive randomization relatively easy.

To prevent between-group variability on relevant baseline characteristics, we use an adaptive or biased-coin randomization algorithm for this trial. Adaptive randomization aims to ensure trial arms are balanced with respect to a priori defined participant factors as well as for the number of participants in each group. Simulation studies show that adaptive randomization provides better balanced trial arms when compared with 'normal' randomization [35] and that it is more efficient in balancing multiple poli-level factors than permutated block stratification [36]. Although not widely used due to organizational complexity, adaptive randomization is a highly effective allocation method, and its wider adaptation in the conduct of randomized clinical trials is recommended [37]. The use of adaptive randomization is supported in the CONSORT statement [38]. We will implement the Pocock & Simon Range Method of adaptive randomization [39], with D = 'range', G is the sum of D (no factor weighting), and P = 0.60.

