### Data analysis

Multiple imputation missing data handling procedures will be implemented using MICE [45] a package for the R Statistical Software Environment. As the quantity of consumed alcoholic drinks is the primary outcome variable in this trial, analysis techniques are chosen that suit the expected data distribution. Baseline measurements of the three trial arms will be compared using t-tests and χ^2^-tests. Trial arm differences on primary and secondary outcome variables at three months are tested using repeated measures ANOVA. Trial arm differences for SOA and TOA between t1 and t2 are tested with a 2 (group) × 2 (time) repeated measures ANCOVA with between and within contrasts. Effect-sizes will be calculated using Cohen's *d *[46]. Trial arm differences on treatment-response will be tested using multiple logistic regression analysis. Costs from TOA and SOA will be derived from cost records of the collaborating SATC. Costs will be assessed in correspondence to the recommendations by the U.S. Panel on Cost-effectiveness in Health and Medicine [25], following a macro-costing approach. QALYs will be calculated from the EQ-5D questionnaire, using algorithm by Dolan [47], retrieved from the Open Health Measures website [48]. Based on these estimations, costs-per-QALY and an incremental cost-effectiveness ratio can be calculated. The U.S. Panel on Cost-effectiveness has recommended that cost-effectiveness studies should conduct sensitivity analysis, which for this cost-effectiveness analysis will be implemented through the bootstrap method [49-51].

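### The prediction that TOA drinking will not change significantly from t1 to t2 takes a non-significant within-arm test as evidence of maintenance, which the (sound) TOA-versus-SOA interaction test does not repair

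*Protocol article*

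**What the plan says.** The Hypotheses section of the protocol article makes three predictions for t1 to t2:

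1. Between arms: TOA participants hold their gains better than SOA participants, "resulting in a significant time (t1–t2) by group (SOA-TOA) interaction".
2. Within SOA: "Alcohol consumption in SOA will be significantly higher at t2 compared to t1".
3. Within TOA: "whereas alcohol consumption in TOA will not change significantly during this period".

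The Data analysis section supplies the test: "Trial arm differences for SOA and TOA between t1 and t2 are tested with a 2 (group) × 2 (time) repeated measures ANCOVA", and the sentence goes on "with between and within contrasts". The first prediction therefore has a matching between-arm test, and the within contrasts are the natural home of the other two.

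The article gives no margin or interval criterion for calling TOA drinking unchanged. It does not say how the three predictions combine, or whether the within contrasts are read only after a significant interaction. The Randomization section aims for 50 participants per arm. The Power calculation section concerns a three-group one-way ANOVA and covers neither the t1-t2 interaction nor the within-arm changes.

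**The concern.** A test that fails to reject no change does not show that there was no change. Stating the TOA prediction as non-significance makes it easier to satisfy as fewer participants are retained, and the Discussion section names attrition as a particular threat to online trials.

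What is at stake is the statement that gains from counsellor-guided therapy last. It concerns alcohol consumption, the primary outcome, at the final follow-up. A report could say that TOA drinking stayed stable when the data are compatible with a real rise.

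**Working it through.** **The plan's own figure.** Table 3 has f = 0.25, three groups, α = 0.05 and N = 159. Then λ = N·f² = 159 × 0.0625 = 9.94, the critical F on 2 and 156 df is 3.054, and power is 0.805. The table reproduces, but it describes a different test from the ones at issue here.

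**Inputs.** From the article: 50 per arm and α = 0.05. Assumed, because the article gives no figure: a two-sided test; 35 or 25 per arm as reduced numbers; and the standardised change dz, which is the mean t1-t2 change divided by the SD of individual changes, over 0 to 0.5. Change scores are taken as normal with equal SD in both arms. The interaction is computed as a two-sample t test on change scores without covariates.

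**Step 1: how often a real TOA rise is non-significant.** The paired t statistic has non-centrality dz·√n. At dz = 0.25:

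| n | dz·√n | Power | Non-significant |
|---|---|---|---|
| 50 | 1.77 | 0.41 | 59% |
| 35 | 1.48 | 0.30 | 70% |
| 25 | 1.25 | 0.22 | 78% |

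At n = 50 the result depends on the assumed rise: 72% non-significant at dz = 0.2 and 21% at dz = 0.4.

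**Step 2: what non-significance leaves open.** The 95% CI half-width is t(0.975, n−1)/√n. At n = 50 this is 2.01/7.07 = 0.28 SD. An observed rise just under 0.28 SD is non-significant, yet its upper limit is just under 0.57 SD.

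**Step 3: does the interaction guard the between-arm conclusion?** Both arms were simulated with the same true rise (200,000 runs, n = 50):

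| dz in both arms | SOA significantly up, TOA not | Interaction significant for TOA | Both together |
|---|---|---|---|
| 0.1 | 9% | 2.5% | 1.7% |
| 0.25 | 24% | 2.5% | 2.4% |
| 0.4 | 17% | 2.5% | 2.1% |
| 0.5 | 6% | 2.5% | 1.3% |

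It does. With the interaction required, false confirmation stays at or below about 2.5%, and also at n = 35 and n = 25.

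**Step 4: does the interaction guard the TOA statement?** Now TOA truly rises, and SOA rises more (n = 50):

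| True dz, SOA / TOA | Interaction significant | All three predictions met | Ratio |
|---|---|---|---|
| 0.5 / 0.25 | 23.5% | 21.5% | 0.215/0.235 = 91% |
| 0.4 / 0.2 | 16.6% | 16.0% | 0.160/0.166 = 96% |

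It does not. In the first row TOA is non-significant in 59% of all trials, but in at least 91% of those with a significant interaction. Selecting on the interaction favours trials in which the observed TOA change happened to be small, so the mislabelling becomes more frequent.

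**The case against.** The strongest case against the point has four parts.

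- **The between-arm test is already there.** This stands. A reader who takes the two within-arm predictions alone might infer that low power counts as success and that equal relapse would confirm the maintenance hypothesis in 16% to 25% of trials (dz 0.20 to 0.40). The article does not support that reading. The sentence just before them requires a significant interaction, and the Data analysis section tests it. Step 3 gives the relevant error rate.
- **Low power works mainly against the hypothesis.** This also stands for the hypothesis as a whole. With a true SOA rise of dz = 0.4 and no TOA change, the interaction is significant in 51% of trials and all three predictions are met in 46%. Only the TOA prediction gets easier as numbers fall.
- **An expectation is not a decision rule.** This is partly right. The text sits under Hypotheses, and nowhere is within-arm significance made the criterion for declaring maintenance. But a hypothesis worded in terms of significance will be reported as supported or not on that basis, and the planned within contrasts would supply the result.
- **Assumed inputs and detail left to an analysis plan.** The dz values and reduced numbers are assumptions. Multiple imputation is planned, so a paired test on 35 completers only stands in for lost information. Confidence intervals are commonly left to the analysis plan. Here, though, the article does more than leave a gap: it states non-significance as the expected result for TOA.

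**Conclusion.** The TOA-versus-SOA comparison of maintenance is well founded. It rests on the interaction, and equal relapse would falsely confirm the full hypothesis in about 2.5% of trials or fewer.

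The flaw is confined to the separate statement about TOA. Non-significance is weak evidence of stability at this sample size: a true rise of 0.25 SD of the change score would pass as no significant change in 59% of trials with 50 per arm and in 70% with 35. A significant interaction does not remove the problem, because it answers whether SOA rose more, not whether TOA stayed where it was.

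The percentages rest on the assumed dz, a two-sided 5% test, and normal change scores. The logical point does not depend on them.

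**What to change.** Reword one hypothesis and one analysis sentence:

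- Rest the maintenance conclusion on the TOA-SOA difference in t1-t2 change (the interaction), reported with its 95% CI.
- Drop the significant-rise and no-significant-change predictions as evidence, and report each arm's t1-t2 change as an estimate with its 95% CI.
- Claim that TOA maintains its gains, taken on its own, only if the upper 95% limit of the TOA rise lies below a margin in units per week that the sponsor fixes before the data are seen.

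No extra data are needed. The cost is that the stand-alone claim becomes harder to make. With 50 per arm and a truly unchanged TOA mean, the upper limit would lie on average at about 0.28 SD of the change score, so a margin of that size would be met in only about half of trials. If the sponsor does not want to set a margin, the first two changes suffice and the stand-alone claim is left out.

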### Measurement instruments

Several measurement instruments are included in the t0, t1 and t2 questionnaire, as presented in Table 2. Alcohol consumption will be measured using substance use subscales of the 'European Addiction Severity Index' (EuropASI) [15] and Timeline-Follow-Back for alcohol consumption [16]. This Timeline-Follow-Back method has good capacity to retrieve drinking history in the past week [17]. As a third scale to measure alcohol consumption burden the AUDIT is included [18].

**Table 2 T2:** Measurement instruments

**Instrument**	**t0 measure**	**t1 measure**	**t2 measure**
EuropASI (subscales)	x	x	x
Timeline-follow-back	x	x	x
AUDIT	x	x	x
QOL	x	x	x
EQ-5D	x	x	x
WAI-work	x	x	x
SF-HLQ	x	x	x
BSI	x	x	x
MCSDS	x		
Dutch mental health thermometer		x*	x*
WAI		x*	x*

Quality of life will be measured using two instruments: The EQ-5D [19-21] and the QOL [22]. The EQ-5D is a highly accepted, widely used and easy to administer instrument for measuring quality of life for alcohol and drug dependents [23,24]. As the scoring algorithm of the EQ-5D generates an index weighted by a preference measure, EQ-5D scores can be used in cost-effectiveness analysis to estimate QALYs [25]. However, it is recommended that the EQ-5D is used in combination with other quality of life instruments. This should be done to minimize its potential limitation in sensitivity until further results confirm EQ-5D validity in alcohol dependent individuals [26]. Therefore, the 'Quality Of Life' scale QOL [22] is included. According to content validity analysis, this is a valid instrument for measuring quality of life across patient groups and cultures. It is conceptually distinct from health status or other causal indicators of quality of life [27].

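### The economic analysis does not keep to one comparator: the aim names the waiting list, but the cost-per-QALY question, hypothesis and analysis name only SOA and TOA

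*Protocol article*

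**What the plan says.** The places below are all in the protocol article.

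- **Aims of the trial.** The comparator is explicit: "This study aims to test the effectiveness and cost-effectiveness of SOA and TOA against a waiting list control group". The same paragraph adds "Incremental cost-effectiveness ratios for SOA and TOA will be calculated", in the plural and without naming a comparator in that sentence.
- **Research questions, Q2.** "What are the comparative costs per quality adjusted life year (QALY) for SOA and TOA". The waiting list is absent here, although each of Q1a to Q1f names it.
- **Hypotheses, question 2.** The authors expect "from t0 to t1 both the costs and the gains in QALY for SOA to be lower" than those of TOA. They conclude that "both the numerator and the denominator of the cost-effectiveness equation is larger for TOA compared to SOA", and so take no position on which programme the incremental calculation will favour.
- **Data analysis.** "Costs from TOA and SOA will be derived from cost records of the collaborating SATC". From these costs and the EQ-5D QALYs, "costs-per-QALY and an incremental cost-effectiveness ratio can be calculated". This lists cost per QALY separately from one incremental ratio, and no comparator is given for either.
- **Measurement instruments.** "EQ-5D scores can be used in cost-effectiveness analysis to estimate QALYs", and Table 2 schedules the EQ-5D at t0, t1 and t2 with no arm excluded.
- **Trial flow.** The waiting-list arm is introduced to TOA only after t1.

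**The concern.** The aim, the research question, the hypothesis and the analysis are all stated, and they do not agree on what the programmes are compared with. An analyst who followed Q2 and the Data analysis section to the letter could leave the waiting list out of the economic evaluation and so not deliver the stated aim.

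There is also a possible bias. If a programme's cost per QALY uses its own change since t0, nothing controls for time. Participants enter because of high drinking (AUDIT above 8 and more than 14 units a week, Table 1) and are recruited mainly through a treatment centre's website. Some improvement without treatment is therefore plausible. Selection is on drinking and not on EQ-5D, so the size of any shared EQ-5D change is unknown. Whatever its size, it would enter the denominator as if the programme had produced it. Even a programme with no effect would then receive a finite cost per QALY.

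**Working it through.** The article states no cost, utility, QALY gain or ratio, so there is no figure to reproduce. The check has two parts.

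**1. Which ratio does the hypothesis describe?** It gives each programme its own numerator and denominator. Three ratios could be meant:

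- TOA minus SOA. This has a single numerator and a single denominator, so it does not fit the sentence.
- Each programme's cost over its own t0–t1 gain. This fits the sentence, the t0-to-t1 wording, and the separate listing of cost per QALY in Data analysis.
- Each programme against the waiting list. This also fits the sentence, and it fits the aim. It needs the waiting list's QALYs, which Q2, its hypothesis and Data analysis never mention.

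The second reading is the natural one, and the third cannot be excluded.

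**2. What would the second reading do?** Let C be programme cost, e the true QALY gain over the waiting list, and s the gain shared by all arms (the waiting-list gain).

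- Ratio on own gain: C / (s + e)
- Ratio against the waiting list: C / e
- First divided by second: e / (s + e), which is (own gain − waiting-list gain) / own gain

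If s = e, the factor is 1/2.

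Illustration, with every input assumed: cost 100 (SOA) and 600 (TOA) in arbitrary units; utility effect over the waiting list 0.02 (SOA) and 0.05 (TOA); linear change over 0.25 year, so QALY gain = 0.5 × 0.25 × utility change.

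With a waiting-list utility change of 0.02:

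- SOA on own gain: 100 / (0.125 × 0.04) = 20,000. Against the waiting list: 100 / (0.125 × 0.02) = 40,000. Factor 0.50.
- TOA on own gain: 600 / (0.125 × 0.07) = 68,571. Against the waiting list: 600 / (0.125 × 0.05) = 96,000. Factor 0.71.
- TOA versus SOA: (600 − 100) / (0.125 × 0.03) = 133,333. The shared change cancels.

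| Waiting-list utility change | SOA, own gain | TOA, own gain | TOA/SOA, own gain |
|---|---|---|---|
| 0 | 40,000 | 96,000 | 2.40 |
| 0.01 | 26,667 | 80,000 | 3.00 |
| 0.02 | 20,000 | 68,571 | 3.43 |
| 0.03 | 16,000 | 60,000 | 3.75 |
| 0.04 | 13,333 | 53,333 | 4.00 |

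In every row the ratios against the waiting list stay at 40,000 and 96,000 (TOA/SOA 2.40), and TOA versus SOA stays at 133,333. The programme with the smaller effect is flattered more.

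**Can the ranking reverse?** Under some inputs it can. Take gains e of 0.02 (SOA) and 0.08 (TOA), s = 0.02, and TOA costing k times SOA. Against the waiting list, TOA/SOA = k × 0.02 / 0.08 = 0.25k. On own gain it is k × 0.04 / 0.10 = 0.40k. With k = 3 these are 0.75 and 1.20, so the order changes. With these gains that happens only for k between 2.5 and 4. In the table above, where the cost ratio is 6, the order does not change.

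**The case against.** A reader might infer that the plan fixes an uncontrolled ratio for each arm and that cost-effectiveness against the waiting list will go unanswered. The article does not support that. It nowhere defines the gains as uncontrolled, and the sentence with the numerator and denominator goes on to speak of an incremental calculation. Both the abstract and the aims promise incremental ratios in the plural, and the aims do so in the paragraph that names the waiting list. Two ratios, each against the waiting list, would fit. Taking costs only from the two programmes is neutral, since the waiting list has no programme cost before t1. The t0–t1 window of the hypothesis is also exactly the period in which that arm is untreated.

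Two further points limit the consequences. Shared improvement cancels in a TOA-versus-SOA ratio. And Q1b and Q1e compare the programmes with the waiting list on secondary outcomes, which include the EQ-5D, so a programme with no EQ-5D effect would be examined there.

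All of this stands, and it makes the own-gain formula an inference. It does not remove the inconsistency: the comparator in the aim is not carried into Q2, its hypothesis or Data analysis. A TOA-versus-SOA ratio cannot say whether SOA is worth offering over nothing, and an EQ-5D comparison alone gives no cost per QALY. A condensed article may leave baseline adjustment and bootstrap detail to a fuller document. That is not the complaint here, which is that the stated passages disagree.

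**Conclusion.** The point holds as an inconsistent and unfixed comparator. The stated aim requires ratios against the waiting list; the passages that put it into operation name only SOA and TOA.

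The bias is conditional. If the separate cost-per-QALY figures use each arm's own t0–t1 gain, they are too low by the factor (own gain − waiting-list gain) / own gain whenever the waiting list also improves. That is one half for SOA if the shared gain equals its true gain. With the assumed inputs and a waiting-list utility change of 0 to 0.04, the factor runs from 1 to 0.33 for SOA and from 1 to 0.56 for TOA. A change in the ranking of the programmes is possible but depends on the inputs chosen. None of these values comes from the article. A TOA-versus-SOA ratio is not biased by shared improvement, but it leaves the comparison with no treatment open.

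**What to change.** In Q2 and in Data analysis, name the comparator of each ratio. For t0 to t1, while the waiting list is untreated, estimate incremental costs and incremental QALYs for three contrasts: SOA versus waiting list, TOA versus waiting list, and TOA versus SOA. Use the EQ-5D already scheduled at t0 and t1 in all arms, and include the waiting list in the planned bootstrap. The waiting list's SOA or TOA programme cost is zero in this window; if other costs are counted, count them in all three arms. Do not present an arm's cost over its own gain as a cost-effectiveness result. Bring the wording of the question 2 hypothesis into line.

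This changes analysis wording only and needs no new data. The price is that cost per QALY may come out less favourable and less precise.
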